**Risk factors for NPH**			
*Hypertension*	Ever had a diagnosis of hypertension or hypertensive disorder or prescribed antihypertensive drugs before or on or up to three months after index date	CRIS	MedCat NLP application and drug search in medical records
*Ischaemic heart disease*	Ever had a diagnosis of ischaemic heart disease before or on or up to three months after index date	CRIS	MedCat NLP application in medical records
*Schizophrenia*	Ever had a diagnosis of schizophreniform disorder before or on or up to three months after index date, as structured ICD10 codes F20–29	CRIS	Medical records
*Diabetes mellitus*	Ever had a diagnosis of diabetes mellitus or prescribed diabetic medication before or on or up to three months after index date	CRIS	MedCat NLP application used on free text in medical records
*Cerebrovascular disease*	Ever had a cerebrovascular accident or diagnosis of transient ischaemic attack or prescribed anticoagulants before or on or up to three months after index date	CRIS	MedCat NLP application used on free text in medical records

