## Introduction

### Normal Pressure Hydrocephalus

Normal pressure hydrocephalus (NPH) is a progressive, potentially treatable condition causing dementia. NPH is characterised by gait disturbance, cognitive impairment, and urinary incontinence. NPH involves a build-up of cerebrospinal fluid (CSF) in the brain (‘hydrocephalus’)
^
1
^ among people aged 60 years and above
^
2
^. Idiopathic NPH is thought to have no clear trigger, while secondary NPH is associated with causes such as trauma, meningitis, stroke, and subarachnoid haemorrhage
^
3
^. In clinical practice, decompensated, longstanding congenital hydrocephalus in older age may be indistinguishable from true idiopathic NPH
^
4
^. In this study, we will particularly focus on idiopathic NPH, while recognising the complexity around its nomenclature
^
2
^, and the difficulty in distinguishing between late-decompensating congenital hydrocephalus and true idiopathic cases. In this protocol, we will use the term ‘NPH’ to refer to cases of NPH without an immediate or clear preceding cause.

NPH is diagnosed according to International or Japanese criteria, which are the two major diagnostic systems for NPH
^
3,
5
^. In the latest guidelines
^
5
^, ‘possible’ NPH relies on a clinical history of at least one of cognitive impairment, gait dysfunction, or urinary incontinence, in the absence of a more likely diagnosis, as well as supportive radiological features and investigations. To diagnose ‘probable’ NPH
^
5
^, a normal opening CSF pressure on lumbar puncture, in the presence of either supportive physical examination and imaging findings or objective improvement in gait following removal of a small volume of CSF, known as a ‘tap test’, are also required. ‘Definite’ NPH is diagnosed following a positive response to treatment, which is variably defined. There is ongoing controversy regarding NPH’s definition as a cohesive clinical entity
^
6
^. This is partly due to the confirmation of ‘definite’ NPH relying on treatment response
^
5
^, and the lack of specific pathognomonic pathological findings on post-mortem studies
^
6
^.

Though the pathophysiology of NPH is unknown, there is a growing understanding of the contribution of vascular disease to its aetiology. Alteration in the cerebral vasculature caused by hypertension, a known risk factor for NPH
^
7
^, leads to reduced arterial pulsatility and increased vessel stiffness
^
8

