**Outcomes**			
*Diagnosis of NPH*	ICD10 code G91.2 or context-confirmed description of diagnosis of NPH in medical record	CRIS or HES or ONS	Medical record
*Dementia diagnosis*	ICD F00-03 diagnosis on or closest after index date	CRIS or HES or ONS	Medical record
*Cognitive trajectory*	All additional recorded MMSE scores at least three months after index MMSE, until censoring occurs	CRIS	Medical record
*All cause mortality*	First date of death recorded after index date	CRIS	Medical record
*Cause of death*	Recorded primary cause of death based on death certificate	ONS	ONS data
*Hospitalisation profile*	Date and diagnosis associated with hospital episode	HES	Medical record

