### Descriptive analyses

We will calculate the period prevalence of recorded diagnoses of NPH in our sample, as defined in
Table 2. We will define NPH diagnosis as ICD10 code G91.2 recorded in CRIS or HES or ONS, or context-confirmed NPH recorded in CRIS.

We will describe the distribution of imaging features of NPH in this population and produce summary statistics. This will include examining for normality and calculating the mean or median of these measures in the population. We will visualise the data and categorise the data into quartiles or quintiles, where appropriate. We will take a dimensional approach, considering these measures as continuous and categorical variables.

We will examine the association between CA and other brain measures of NPH. We will examine the association between imaging features of NPH and markers of neurodegeneration, such as cortical atrophy and hippocampal volume. We will describe the period prevalence of imaging features suggestive of NPH, based on reported cut-offs.

We will describe variation in CA and other imaging features of NPH according to demographics, covariates, and risk factors for NPH (see
Table 2).

We will describe imaging features of NPH in relation to recorded diagnosis of NPH. We will describe the relationship between imaging features and diagnosis of NPH, including whether a clinically useful threshold exists. We will build several models to examine individual imaging features of NPH and combinations of features, to assess for possible additive effects of these. In addition, we will compare clinical radiological reports, which are available in the free text notes of CRIS, with imaging features of NPH to look for concordance of these findings and to determine what role the imaging report played in future management of these cases.

We will examine for systematic differences based on EHR data between individuals with and without imaging data in the cohort using logistic regression.

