### Potential further analyses

Depending on our initial exploratory findings, we will consider additional analyses. If we have sufficient cases of individuals with imaging features of NPH, we plan to undertake additional statistical analyses, such as Cox regression with time to mortality or dementia diagnosis as outcomes.

If we have sufficient cases, we will describe NPH imaging features in relation to outcomes such as hospitalisation, mortality, cognitive decline, and dementia diagnosis. We will describe hospitalisation profiles (eg. falls, surgery) in relation to NPH imaging features. We will look at factors associated with subsequent diagnosis compared to no diagnosis among people with imaging features of NPH.

If, as expected, we find few cases of NPH, we will define NPH ‘imaging cases’ based on the presence of suggestive imaging features and their relationship with NPH diagnosis, and consider a nested case-control study. We will assess for differences in risk factors, demographics, and clinical covariates (see
Table 2) between cases and controls using logistic or categorical regression.

We plan to test our measures in low-field MRI
^
72
^, and we will consider comparing our findings in other datasets
^
73
^.

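### Table 2 counts any anticoagulant prescription as cerebrovascular disease, which puts false positives into one exploratory risk factor

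*Protocol article*

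**What the plan says.** The cerebrovascular row of Table 2 (Risk factors for NPH) reads: "Ever had a cerebrovascular accident or diagnosis of transient ischaemic attack or prescribed anticoagulants before or on or up to three months after index date". Its method of measurement is "MedCat NLP application used on free text in medical records". The clause at issue is the last one, "or prescribed anticoagulants before or on or up to three months after index date". No indication for the drug is required, and no narrower version of the variable is mentioned.

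The ischaemic heart disease row is based on diagnosis only: "Ever had a diagnosis of ischaemic heart disease before or on or up to three months after index date". Hypertension and diabetes, and depression under Clinical covariates, each accept either a diagnosis or symptom record or a relevant prescription.

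The variable enters the analysis in three places:

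- Descriptive analyses: "We will describe variation in CA and other imaging features of NPH according to demographics, covariates, and risk factors for NPH". The Aims and objectives section also plans to describe how recorded NPH relates to risk factors.
- Study design: risk factors for NPH are listed among the possible covariates. The Analysis plan leaves the choice of confounders, effect modifiers and mediators to directed acyclic graphs.
- Potential further analyses, for a nested case-control study that is only under consideration: "We will assess for differences in risk factors, demographics, and clinical covariates", by logistic or categorical regression.

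**The concern.** The three criteria are joined by *or*, so an anticoagulant prescription with no stroke or TIA on record still makes a person positive. It is general clinical knowledge, not something the article states, that these drugs are also given for heart-rhythm and venous clotting indications. In a cohort aged 60 and over, some people will therefore be flagged who have no cerebrovascular disease.

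The Introduction makes vascular disease a substantive interest: "there is a growing understanding of the contribution of vascular disease to its aetiology". It also names stroke among the causes of secondary NPH, while the study focuses on NPH without a clear preceding cause. This is the Table 2 risk factor that records stroke, so its meaning matters. If it mixes stroke or TIA with treatment for other conditions, a weak or absent association cannot be read as evidence about cerebrovascular disease.

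**Working it through.** No figure in the article depends on this variable, so there is nothing to reproduce. The sample size calculation uses only callosal angle means and standard deviations. What follows illustrates the size of the effect.

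**Inputs.** NPH prevalence of about 1% is from the article (Memory services). The rest are assumptions, because the article gives no values: true stroke/TIA prevalence *p* = 10-20% of the cohort; anticoagulant without stroke/TIA *a* = 5-15% of the cohort; NPH risk 2% with stroke/TIA and 1% without. The true odds ratio is then (0.02/0.98)/(0.01/0.99) = 2.02. Two further assumptions are that all stroke/TIA is captured and that anticoagulant-only people carry the 1% risk.

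**Step 1, false positives.** Share of flagged people who truly have the disease: PPV = *p*/(*p* + *a*). Risk in the flagged group = PPV × 2% + (1 − PPV) × 1%. Observed odds ratio = flagged odds divided by 0.01/0.99 = 0.010101.

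| *p* | *a* | PPV | Flagged risk | Observed OR |
|---|---|---|---|---|
| 10% | 15% | 0.10/0.25 = 40% | 1.40% | 0.014199/0.010101 = 1.41 |
| 20% | 15% | 0.20/0.35 = 57% | 1.57% | 0.015965/0.010101 = 1.58 |
| 10% | 5% | 0.10/0.15 = 67% | 1.67% | 0.016949/0.010101 = 1.68 |
| 20% | 5% | 0.20/0.25 = 80% | 1.80% | 0.018330/0.010101 = 1.81 |

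**Step 2, a second parameterisation.** Let *f* be the share of people *without* stroke/TIA who take an anticoagulant, assumed 3-15%, with overall NPH prevalence held at 1%. Then PPV = *p*/(*p* + (1 − *p*)*f*), running from 0.10/0.235 = 43% to 0.20/0.224 = 89%. A true odds ratio of 2.0 is observed as 1.42-1.89, and one of 1.5 as 1.21-1.45.

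**Step 3, use that differs by NPH status.** Take *p* = 15% and a true odds ratio of 1.0. The flagged share in each group is *e* = *p* + (1 − *p*)*f*. With *f* = 10% in non-cases, *e* = 0.235 and the odds are 0.307.

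- *f* = 20% in cases: *e* = 0.320, odds 0.471, observed odds ratio 1.53.
- *f* = 5% in cases: *e* = 0.1925, odds 0.238, observed odds ratio 0.78.

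A null association can therefore move in either direction. Nothing in the article shows that use does differ by NPH status.

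**Step 4, scale against sampling error.** Table 3 expects 50 NPH cases in the imaging subset. If 25% are flagged (10% + 15%, or 20% + 5%), the case cells are 12.5 and 37.5. The standard error of the log odds ratio is then about √(1/12.5 + 1/37.5) = 0.327, and the 95% limits lie a factor exp(1.96 × 0.327) = 1.9 either side. In the full cohort, 20,000 × 1% = 200 cases gives √(1/50 + 1/150) = 0.163 and a factor of 1.38. The largest shift in step 1 is a factor of 2.02/1.41 = 1.43.

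**The case against.** The strongest case against has five parts.

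- **Drug proxies are the table's usual pattern.** Hypertension, diabetes and depression all use one, and ischaemic heart disease is the exception. This stands. A reader might infer from the ischaemic heart disease row that Table 2 contradicts itself, but the contrast does not support that. The sound argument is only that this drug class does not point specifically to this disease.
- **The variable is not a fixed confounder.** A reader might infer that misclassification leaves residual confounding in the imaging models. The article names risk factors only as possible covariates and defers selection to directed acyclic graphs, so no adjustment model is fixed. The inference is not supported.
- **The broad rule may recover missed cases.** The article gives no sensitivity of the language-processing tool for stroke or TIA, and it warns under Strengths and limitations that routine data may be incomplete. A deliberate trade for sensitivity is plausible, though the article does not state it. This bears on the fix but does not make the proxy specific. For the outcome, free-text records must be confirmed from context ("ICD10 code G91.2 or context-confirmed description of diagnosis of NPH in medical record"). No such step is stated for this exposure.
- **The model favours its own conclusion.** It assumes perfect capture of stroke/TIA and no excess NPH risk in anticoagulant-only people. If that group carries some vascular excess risk, attenuation is smaller than shown. This stands, and the range must be read as conditional.
- **Imprecision exceeds the bias.** With 50 cases the interval is wider than the shift. With 200 cases the two are of similar size at the unfavourable end. Imprecision does not remove bias, but it limits the practical effect in the imaging subset.

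**Conclusion.** The point holds as a non-specific proxy in one exploratory risk factor, and it is minor. Applied as written, the rule will label some people as having cerebrovascular disease who do not have it. The likely direction is attenuation. Bias either way is possible if anticoagulant use differs by NPH status.

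The size cannot be fixed from the article. The illustration, a true odds ratio of 2.0 appearing as about 1.4-1.8, rests on assumed prevalences, an assumed true effect, complete capture of stroke/TIA and baseline risk in anticoagulant-only people.

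A reader might infer that the main results are at risk. They are not: the primary outcome, the period prevalence of NPH, the callosal angle comparison between diagnoses and the sample size do not use this variable, and the Analysis plan calls the study primarily descriptive and exploratory.

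**What to change.** In Table 2, define cerebrovascular disease primarily by a recorded stroke or TIA. Hold anticoagulant use as a separate variable. Report the current broad definition as a sensitivity analysis, so that readers can see whether the result depends on the drug criterion. State how prescriptions are found, since the hypertension row names a drug search and this row does not.

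The data are retrospective and nothing new has to be collected, so the cost is an edit to one row and one further run of the affected analyses. The downside is that true cases missed by the language-processing tool, and identifiable only through treatment, drop out of the primary definition. The article does not allow their number to be estimated, which is why the broad definition should be kept as a sensitivity analysis.

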**Outcomes**			
*Diagnosis of NPH*	ICD10 code G91.2 or context-confirmed description of diagnosis of NPH in medical record	CRIS or HES or ONS	Medical record
*Dementia diagnosis*	ICD F00-03 diagnosis on or closest after index date	CRIS or HES or ONS	Medical record
*Cognitive trajectory*	All additional recorded MMSE scores at least three months after index MMSE, until censoring occurs	CRIS	Medical record
*All cause mortality*	First date of death recorded after index date	CRIS	Medical record
*Cause of death*	Recorded primary cause of death based on death certificate	ONS	ONS data
*Hospitalisation profile*	Date and diagnosis associated with hospital episode	HES	Medical record

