**Results:**

We will estimate the period prevalence of NPH in this population. We will evaluate automated measurement tools for imaging features of NPH, describe their distributions, and their variation by covariates (eg. demographics). We hypothesise that people with a diagnosis of NPH will have smaller CA compared to people with a diagnosis of dementia, and that imaging features of NPH will predict future diagnosis of NPH. Depending on our findings, we may undertake more detailed analyses, such as a nested case-control or survival analysis.

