**Imaging parameters**			
*CA measure*	Angle between medial walls of lateral ventricles on date of scan, in degrees, measured using algorithm. When measured manually, this will be defined as the angle of the corpus callosum at the level of the posterior commissure, at the plane perpendicular to the anterior commissure-posterior commissure line, by convention ^ 29 ^.	SLaM Image Bank	MATLAB algorithm and manual measurement
*Ventricular volume*	Volume of right and left lateral ventricle in mm ^3^ on date of scan, derived from segmentation data	SLaM Image Bank	SynthSeg output
*White matter hyperintensity (WMH) volumes*	Binary mask of WMH locations and volume measures (mm ^3^). This will be further segmented into periventricular region WMHs.	SLaM Image Bank	WMH-SynthSeg output
*Other imaging features*	Segmentation values for hippocampal, intracranial, extra-ventricular CSF volumes in mm ^3^ on date of scan	SLaM Image Bank	SynthSeg output
*Potential additional features*	EI, z-EI, CSF volume at high convexity region and Sylvian fissures	SLaM Image Bank	Pipelines developed from SynthSeg output

To measure CA, we will extract the ventricles from SynthSeg segmentations. [name]
*et al.*
^
34
^, who originally developed an algorithm calculating CA automatically, are collaborators on this project and have kindly shared their code, developed in MATLAB, for use in this study. This tool is not under copyright and the developers of the tool are co-authors on this protocol. This algorithm calculates the angle between the medial walls of the ventricles to approximate CA. We will test this algorithm in our population and, if necessary, adapt it.

We will run WMH-SynthSeg to automatically assess for WMH using T2-weighted (T2-w) or FLAIR MRIs
^
63
^. WMH-SynthSeg has previously been shown to identify WMHs with high accuracy compared to manual delineation (r=0.84, p < 0.001), even in a cognitively-impaired population, as well as showing a stepwise association with manually-derived Fazekas score
^
64
^. We will validate WMH-SynthSeg output against manual measurements, and undertake visual quality control assessment of both T2-w or FLAIR images and WMH-SynthSeg output.

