### Study design

We will assemble a retrospective cohort study using SLaM’s CRIS data platform. The study population will be all people aged 60 years and above with at least one referral to memory services recorded over the study period 2007–2024. We expect at least 20,000 participants in this cohort. We will extract relevant anonymised retrospective patient data from CRIS for the entirety of the cohort and specify the data extraction date. We will examine CRIS data and use linkage data to HES, ONS, and imaging data.

A subset of this cohort will have linked T1-w, T2-w, and FLAIR brain MRI scans that have been collected as part of routine clinical care over the period 2008–2021. We expect to have at least 5,000 people in this sample, based on the number of scans currently available, however the sample size is subject to change as these datasets are live.

*Inclusion criteria:*

Aged at least 60 years at time of memory clinic referralReferral to memory services, recorded in CRISPeople who are referred but do not attend a review will be included and compared with those who do attend, though they may have limited data

*Exclusion criteria:*

Nil

*Cohort entry date:*

Date of referral to memory service

*Exit from cohort:* Censored at minimum of

DeathIncident NPH diagnosisEnd of study period

*Covariate assessment window:*

Anytime prior to cohort entry date up to three months after date of first face-to-face or virtual review in memory clinic, inclusive

*Primary outcome:* ICD10 code G91.2 recorded in CRIS
*or* HES
*or* ONS,
*or* context-confirmed NPH recorded in CRIS

*Possible secondary outcomes:*

MortalityHospitalisation profileDementia diagnosisCognitive trajectorySymptoms of NPH (eg. falls)

*Exposures:*

CA in degreesVentricular volume in mm
^3^
White matter hyperintensities (WMH) volumesOther brain measures to be determined (TBD)

*Possible covariates:*

AgeSexEthnicityIMDRisk factors for NPHCognitionHealth of the Nation Outcome Score (HoNOS)

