### Diagnostic accuracy of CA

We will compare mean or median CA between people with a diagnosis of NPH and other diagnoses, such as dementia and its subtypes, in particular AD, using a two-sample t-test or Mann-Whitney U test.

We will analyse the association between NPH imaging features and NPH diagnosis using logistic regression. If we have sufficient numbers, we will consider using area under the curve (AUC) analysis, and Cox regression for time-to-event analysis. We will consider penalised Cox regression if the number of outcome events is small, as we expect.

If we have enough cases, we will calculate the sensitivity, specificity, positive, and negative predictive values for identifying recorded NPH in this population using CA. Estimated numbers for this are in
Table 3.

**Table 3. T3:** Expected values of cases of NPH picked up on screening in CRIS (based on initial searches undertaken in March 2022). Based on total population of 5,000 individual patient scans and an expected prevalence of approximately 1% of dementia cases
^
71
^. Figures are based on previous sensitivity (97%) and specificity (88%) measures using a cut-off of <90 degrees
^
31
^.

True iNPH cases				
Callosal angle <90		+	-	Totals
	+	49	582	631
	-	1	4268	4269
	Totals	50	4850	5000

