### Sample size and power calculation

In initial feasibility searches carried out in March 2022, keyword search for ‘hydrocephalus’, excluding ‘no hydrocephalus’, yielded 896 records. Validation of a subsample gave a total number of 251 cases of potential NPH, based on examination of the context. Feasibility counts show 136 patients aged >50 with a shunt in CRIS.

Using STATA V16.1, we calculated the sample size required to test for a difference in means using a two-sample t-test. Measures were based on the following expected means and standard deviations (SD) for CA
^
31
^:

NPH = 66 (SD= 14)

AD = 104 (SD= 15)

To test for a difference with 90% power and an alpha level of 0.05, we calculated a required sample size of 10, with 5 in each group. Based on initial feasibility counts, we should have ample cases in our sample to estimate this expected difference in mean CA. With a conservative estimate of 49 cases of NPH, we should have 90% power to detect a minimum difference of 10° in mean between NPH and AD groups.

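### No rule places the scan before the NPH diagnosis or shunting, so the CA comparison, accuracy and prediction analyses would count people already diagnosed or shunted as NPH cases

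*Protocol article*

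**What the plan says.** All references are to the protocol article.

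- **Outcome.** Table 2 (Outcomes) defines NPH as "ICD10 code G91.2 or context-confirmed description of diagnosis of NPH in medical record". The Clinical data, Study design and Descriptive analyses sections repeat the definition, and none adds a date.
- **Other variables in the same table.** These are dated. Dementia is "ICD F00-03 diagnosis on or closest after index date". Risk factors have a limit, for example "Ever had a diagnosis of ischaemic heart disease before or on or up to three months after index date".
- **Exposure.** Table 2 (Imaging parameters) defines CA as "Angle between medial walls of lateral ventricles on date of scan, in degrees, measured using algorithm". Scans are routine ones from 2008–2021.
- **Cohort.** Under Study design, entry is "Date of referral to memory service", the exclusion criteria are nil, and follow-up ends at death, incident NPH diagnosis or the end of the study period.
- **Analyses.** Diagnostic accuracy of CA states: "We will compare mean or median CA between people with a diagnosis of NPH and other diagnoses". It then lists logistic regression, possible AUC and Cox analyses, and sensitivity, specificity and predictive values. Descriptive analyses adds a search for a clinically useful threshold. No timing rule is attached to any of these.
- **Hypothesis.** The abstract expects that "imaging features of NPH will predict future diagnosis of NPH".
- **Shunts.** Sample size and power calculation reports: "Feasibility counts show 136 patients aged >50 with a shunt in CRIS".

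**The concern.** Two different things can go wrong when the order of scan, diagnosis and shunt is left open.

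The first is temporal. If NPH was already recorded when the scan was made, the scan cannot predict a future diagnosis. Such a person adds to the apparent association without bearing on the abstract's hypothesis.

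The second is anatomical. The Introduction describes a shunt as a tube placed into the brain to divert CSF. CA is measured between the medial walls of the lateral ventricles, and ventricular volume is a further exposure. A scan made after shunting therefore measures a system on which treatment has already acted. The Introduction also says that definite NPH is established by response to treatment, so the most certain cases are treated ones.

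At stake are the estimated NPH–AD difference in CA, the accuracy figures, any threshold drawn from them, and the reading of the regression models as prediction. The Introduction envisages decision-support tools for use before treatment, so a threshold derived partly from treated anatomy would be a poor basis for them.

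**Working it through.** **1. The plan's own sample size reproduces.** Inputs (Sample size and power calculation): NPH mean 66, SD 14; AD mean 104, SD 15; power 90%; alpha 0.05, taken as two-sided. A two-sample t-test with unequal SDs (noncentral t, Satterthwaite degrees of freedom) gives 86.7% power at 4 per group and 95.0% at 5 per group, so 5 per group is right. With 49 per group, power for 10 degrees is 92.2%, so that statement is right too. The problem is not one of power.

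**2. What each passage does to the order of events.**

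| Element | Date condition |
|---|---|
| NPH outcome | none |
| Dementia outcome | on or after index date |
| Risk factors | up to three months after index date |
| CA | date of scan, not tied to referral, diagnosis or shunt |
| Cohort entry | referral, not scan |
| Exclusions | none |

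Someone diagnosed and shunted years before the scan meets every condition for being an NPH case in the t-test or Mann-Whitney test, the logistic model, the AUC and the sensitivity calculation. Image quality control removes artefact and poor scans, not scans made after diagnosis or shunting.

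**3. Illustration of size.** The documents give neither the share of NPH scans made after shunting (f) nor the change in CA after shunting (d). Both are assumed here: f from 20% to 50%, and d as a widening of 10 to 30 degrees with the SD unchanged at 14.

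Mean difference = 104 − (66 + f·d).
Sensitivity at CA below 90 = (1 − f)·Φ(24/14) + f·Φ((24 − d)/14), where 24 = 90 − 66.

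- No post-shunt scans: difference 38; sensitivity Φ(1.714) = 0.957. This normal model lies close to the 97% that Table 3 takes from the cited study.
- f = 0.2, d = 10: difference 104 − 68 = 36; sensitivity 0.8 × 0.957 + 0.2 × 0.841 = 0.934.
- f = 0.5, d = 30: difference 104 − 81 = 23; sensitivity 0.5 × 0.957 + 0.5 × 0.334 = 0.645.

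If CA did not widen after shunting, these losses would not arise. Scans made during or after an NPH work-up could instead inflate apparent prediction.

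**4. Cost in cases.** By the t-test calculation of step 1, 23 NPH scans give 89.9% power for 10 degrees against 1,000 AD scans and 90.3% against 3,000. The size of the AD group is an assumption, because the article does not state it.

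**The case against.** The undated definition is right for period prevalence, where known cases must count. The study also shows an interest in incidence: follow-up ends at incident NPH diagnosis, Cox regression is considered, and Potential further analyses looks at subsequent diagnosis among people with imaging features. The aims section speaks of predicting NPH diagnosis without the word future, and known cases are legitimate in a cross-sectional accuracy analysis. The work is described as mainly descriptive and exploratory, the accuracy figures are conditional on enough cases, and a condensed article may leave scan selection to a fuller plan.

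Much of this stands, and it narrows the point. It does not remove it. Incident NPH is not defined, prevalent cases are not removed, and follow-up starts at referral. Censoring could help only the optional Cox model, and the subsequent-diagnosis analysis is itself optional. Nor is this just a detail left out: the Clinical data section says the pre-specified variables are fully defined in Table 2, and that table dates the dementia outcome and the risk factors but not the primary outcome.

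Three stronger readings are tempting but unsupported:

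- A reader might scale the 136 shunted people by the proportion of the cohort with scans and conclude that most NPH scans come from shunted people. The 136 are counted across CRIS, are aged over 50 rather than 60 and above, and are not confirmed as memory-service patients, as NPH, or as scanned after the shunt.
- A reader might infer that sensitivity will certainly be understated. The documents say nothing about CA after shunting.
- A reader might want a pre-shunt rule for all imaging work. The validation and failure analyses ask how the algorithm performs on routine scans, and post-shunt scans belong there.

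**Conclusion.** The point holds for the analyses under Diagnostic accuracy of CA and for the threshold search under Descriptive analyses. As written, these count people scanned after diagnosis or shunting as NPH cases, and they cannot test prediction of a future diagnosis in those people. This conclusion rests on the text alone and needs no assumption about what shunting does to CA.

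The size and direction of any distortion are not in the documents. The illustrated falls, to between 36 and 23 degrees and to between 93% and 65% sensitivity, rest wholly on the assumed share of post-shunt scans and the assumed widening. Detecting that NPH and AD differ in mean CA is not under threat; the estimates, the accuracy figures and the predictive reading are. Period prevalence and the validation of automated against manual CA are unaffected.

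**What to change.** Add a scan-selection rule that applies only to the NPH comparison, regression, AUC, Cox, accuracy and threshold analyses:

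- Use each person's earliest usable scan before any shunt, with the shunt dated from CRIS text or from HES where available.
- For prediction and time-to-event analyses, start follow-up at the scan date, exclude anyone with NPH recorded on or before that date, and define incident NPH accordingly.
- For the cross-sectional comparison and accuracy analyses, keep prevalent unshunted cases but report them separately from incident ones. Present post-shunt scans descriptively only.
- Leave the period-prevalence count and the algorithm validation and failure analyses as they are.

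The cost is protocol wording and date logic on retrospective records. One point needs checking first: Table 2 lists the date and diagnosis of hospital episodes but no shunt variable. Surgery is mentioned among hospitalisation profiles, so dating shunts from HES is plausible but not shown. Some NPH scans will be lost. About 23 remaining NPH cases against a large AD group would still give 90% power for 10 degrees.
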